## Abstract

**Background:**

New technologies, like socially assistive robots (SARs), may have the potential to support caregivers at home. Still, the evidence for people with dementia in home care is unclear because a lot of studies are performed in a laboratory or institutional setting, and mainly use robots in prototype stages.

**Objective:**

This study aims to explore the effects of the refined, commercially-available, humanoid SAR Pepper combined with a tablet PC–based dementia training program (Coach Pepper) versus an exclusively tablet PC–based dementia training program on psychosocial and physical outcomes of people with dementia living at home, including caregivers and dementia trainers. We hypothesize that Coach Pepper has a more positive effect on the primary outcome motivation (stable or decreased apathy) of people with dementia.

**Methods:**

A mixed methods study will be performed, including a randomized controlled, parallel, 2-arm study with a complementary qualitative part. This sample includes 40 PWD living at home and 40 relatives, each complemented with five professional caregivers and dementia trainers. The intervention group will receive Coach Pepper (a SAR connected with a tablet PC–based dementia training program), and the control group will receive exclusively tablet PC–based training without the SAR. The duration of the intervention will be three weeks per household. Data will be collected at baseline and during and after the intervention by standardized questionnaires, sensor data of the robot, and tablet PC, as well as semistructured interviews, focus groups, and observation.

**Results:**

To date, no results are available for this study protocol. The study intervention started in May 2019 and will end in Spring 2020.

**Conclusions:**

The intervention of this study can be seen as a nonpharmacological intervention, including cognitive and physical training by a robot. This study will help to further refine SAR for the specific needs of people with dementia living at home.

**International Registered Report Identifier (IRRID):**

DERR1-10.2196/14927

## Introduction

### Background

Dementia rates are increasing worldwide and consequently burden global health care resources to a serious degree [1,2]. On the other hand, there is a decreasing number of available caregivers to provide (nursing) care [3-5]. (Nursing) care of people with dementia usually takes place at home, especially in the early stages [6]. Owing to the progression of dementia and growing (nursing) care needs because of increasing care dependency (eg, in mobility, social contacts, and learning ability), (nursing) care problems (eg, incontinence and malnutrition), professional care (eg, by nurses) and a possible nursing home transition become increasingly necessary [6-8]. One of the most important aims in (nursing) care for people with dementia is to promote their independence according to their stage of dementia and individual abilities. Such (nursing) care can counteract a galloping progression of care dependency [9]. It is in this context that new technologies, such as socially assistive robots (SARs), may constitute a supportive device for caregivers because they have the potential to promote the independence and well-being of older people [10,11].

SARs can be defined as representing an intersection of assistive robots (giving aid or support to a human user) and socially interactive robots (social interaction through speech and gestures) [12]. The goal of SARs is to create a close and effective interaction with a human user by giving assistance through social interaction (eg, in activities of daily life ranging from cognitive to physical tasks or to encourage emotional expression, conversation, and gestures) [12]. The appearance of the SARs can vary. They can look like a mechanoid with a machine-like appearance, or like a humanoid, such as Pepper by Soft Bank Robotics, which is designed with an unrealistic but still human-like appearance so that users can identify it as a robot. They can also look like an android with an almost realistic human-like appearance, or, in the case of animal-like SAR, can look like an animal, such as Paro, the seal baby [13,14]. In this study, the humanoid SAR Pepper (see section Interventions) is used.

Results of various reviews (literature, scoping, and systematic) show that research on SAR in the context of older people with and without dementia is most often conducted on SAR with an animal-like appearance, such as Paro, which was designed with the appearance and behavior of a baby seal, AIBO, the robotic dog, or NeCoRo, the robotic cat [13,15]. However, there is a wealth of studies relating to other robot types, like humanoid SAR [15,16].

Until now, the effectiveness of SAR in all care settings, especially in-home care, has generally been unspecified. Studies show that these robots may have a positive impact on affect, cognition, physiological parameters, use of medications, social contacts, and quality of life with respect to well-being and behavior [13,15,16]. Regarding behavior, apathy, which is defined as a loss of motivation [17], is one of the most common behavioral and psychological symptoms (BPSD) in people with dementia, with an overall mean prevalence of 49% [18].

Measurements from research studies have demonstrated that people with dementia have lower capacities for motivation processes [19]. Current models of motivation identify and discriminate two phases: (1) goal setting; and (2) goal pursuit. The latter requires self-regulatory capacities for decision-making, regulation of activation, and regulation of motivation. Forstmeier and Maercker [19] concluded from their research that cognitive and physical training should be complemented by motivation-supporting training strategies, such as goal-setting and self-motivation [19]. In addition, motivation-oriented interventions support the reduction of neuropsychiatric symptoms, such as depression and apathy (loss of motivation). The study described in this protocol implemented motivation-oriented strategies into the overall technological Coach Pepper concept in the shape of a humanoid SAR, which worked to motivate the people with dementia by means of social interaction to perform daily dementia training on a tablet PC (all functions of Coach Pepper are shown in Figure 1).

**Figure 1 figure1:**
[figure not shown]
The functions of Coach Pepper.

It is necessary to focus on the motivation of people with dementia, because loss of motivation (apathy) could entail a decline in cognition, problems in activities of daily living (ADL), decreased quality of life, increased morbidity, greater mortality, and for caregivers, a greater caregiver burden [20-22]. In a systematic review by Pu et al [15], only two studies were found which included apathy as an outcome measure of SAR interventions. Only one of these studies included a humanoid SAR as an intervention for people with dementia. None of these two studies were performed in home care, which is a setting where a lack of research with SAR is still prevalent.

In their scoping review, Buhtz et al [23] identified 19 studies that included SAR for care-dependent people at home. Most of these robots were in a prototype stage and were tested mainly for technical aspects and operability in predominantly exploratory or piloting studies. Thus, there is a recommendation to explore the effectiveness of SAR [15,23] in well-designed randomized controlled trials with larger sample sizes [23,24]. In home care, often no more than ten older people with or without dementia are included in studies using SAR [25-28]. This is not surprising, because the home care setting can be seen both in technical and scientific terms as one of the most challenging and complex scenarios for SAR. A household with people and objects that seemingly unpredictably vary their position presents SAR with enormous challenges and hurdles [23]. But research of SAR in home care is extremely important, because many older people with and without dementia would like to live at home as long as possible. SAR, as an innovative intervention, has the potential to support care independency (in various ADL) at home and may help to avoid or delay institutional care (eg, nursing homes).

### Overall Aim

The overall aim is to explore the effects of a humanoid SAR versus an exclusively tablet PC–based dementia training on psychosocial and physical outcomes of people with dementia living at home, including caregivers and dementia trainers.

#### Primary Aims

The primary aims of this study include exploring the effect of Coach Robot Pepper on motivation (in the sense of increased, decreased, or stable apathy) of people with dementia versus the tablet PC–based training, and exploring the effect of Coach Robot Pepper on the care burden of relatives compared with the tablet PC–based training.

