#### Primary Outcome Measurements

##### Motivation

The Apathy Evaluation Scale (AES) will be used to measure motivation because apathy can be understood as a loss of motivation. The scale has 18 items (4-point Likert scale), and a total of 18-72 points can be obtained. Higher scores correspond to a higher degree of apathy, and therefore lower motivation [34,35].

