##### Care Burden

The Zarit Burden Interview will be used to measure the subjective care burden of the relatives. The instrument has 22 items (5-point Likert scale), and a total of 0-88 points can be obtained. Higher scores indicate greater caregiver distress [36-38].

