### Analysis

#### Quantitative Analysis

Statistical analyses of the results will be performed following the intention-to-treat principle. Descriptive statistics of the data will be presented as a mean and standard deviation, or median and quartile, depending on the nature of the distribution. To describe categorical data, absolute and relative frequencies will be used. To answer the primary question as to whether the motivation differs between the two intervention groups, a median regression is planned. Therefore, it can be adjusted for the degree of dementia and depression. For differences between the intervention groups for the secondary outcomes, the ordinal scale data will be analyzed with median regression. For metric data, a covariance analysis is planned, which also adjusts to degrees of dementia and depression. Changes in pre- and postintervention outcomes concerning relatives will be analyzed by a paired *t* test or a two-tailed Wilcoxon signed-rank test, depending on the distribution of the data. For the sensor data, correlations with the scores of questionnaires will be performed. Furthermore, a skeleton-based analysis of human activity will be applied on the video frames of the physical exercises [57]. The estimated increase of kinetic energy of the movements is intended to provide cues for the increase of motivation [58]. In addition, the video data will be analyzed for nonverbal expressive features which provide analytics about the state of mobility. The significance level will be set to alpha=0.05. For the evaluation, SAS 9.4 (SAS Institute Inc, Cary, North Carolina, United States) will be used.

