## Discussion

The overall aim of this study is to explore the effect of a SAR on psychosocial and physical outcomes of people with dementia living at home, including caregivers and dementia trainers. We hypothesize that the robot has a positive effect on the primary outcome motivation (stable or decreased apathy) of people with dementia.

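### The article names one primary outcome in its hypothesis, primary analysis and power statement but two in its aims and measurements, and names no between-group analysis for the second

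*Protocol article*

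**What the plan says.** **One primary outcome.** The abstract's Objective states: "We hypothesize that Coach Pepper has a more positive effect on the primary outcome motivation". The Discussion repeats it: "We hypothesize that the robot has a positive effect on the primary outcome motivation (stable or decreased apathy) of people with dementia". The Quantitative Analysis section describes one primary question, whether motivation differs between the groups, and assigns it a median regression. The Sample Size section discusses power for motivation and does not mention burden.

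**Two primary outcomes.** The Primary Aims section lists motivation and then a second aim, "exploring the effect of Coach Robot Pepper on the care burden of relatives compared with" the tablet-only arm. Primary Outcome Measurements has two entries. Under Motivation: "The Apathy Evaluation Scale (AES) will be used to measure motivation because apathy can be understood as a loss of motivation". Under Care Burden: "The Zarit Burden Interview will be used to measure the subjective care burden of the relatives". The secondary measurements begin only after both.

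**Testing.** The Quantitative Analysis section gives one level for everything: "The significance level will be set to alpha=0.05". For relatives' outcomes it names a pre-post analysis by a paired t test or a Wilcoxon signed-rank test. The article gives no rule for combining the two outcomes.

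**The concern.** The primary outcome decides in advance which result makes the trial positive, and here that depends on the section cited. With a null AES and a favourable Zarit, the Primary Aims and Primary Outcome Measurements sections would support reporting a positive primary result. The abstract's hypothesis and the primary analysis would call the same data a negative trial. Because some participants had already finished when the article was written, the choice could end up being made with results in view.

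The second outcome is also poorly served by its analysis. The aim asks whether burden differs between Coach Pepper and tablet training. A paired test asks whether burden changed over time among the relatives analysed. Both arms receive training, weekly trainer visits and calls, so burden could fall in both arms without any contribution from the robot. A primary claim on burden could then rest on a change that makes no use of the randomised comparison.

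**Working it through.** **1. The plan's own power figure.** Inputs from Sample Size: 20 per group, difference 10, SD 11, two-sided alpha 0.05. Effect size d = 10/11 = 0.909, stated as 0.91. Power from the noncentral t distribution for two groups is 80.1% at d = 0.91 and 80.0% at d = 10/11. The stated 80% reproduces, for one outcome tested at 0.05.

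**2. Primary outcomes by section.**

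| Section | Motivation | Care burden |
|---|---|---|
| Abstract, Objective | primary | not named in the hypothesis |
| Primary Aims | primary | primary |
| Sample Size | power discussed | not mentioned |
| Primary Outcome Measurements | AES | Zarit |
| Quantitative Analysis | the primary question; between-group median regression | covered by name only through the pre-post test for relatives |
| Discussion | primary | not named in the hypothesis |

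**3. False-positive rate under each reading.** The article does not say which applies, so each is an assumption. Each outcome is taken to have a valid between-group test at 0.05.

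- *AES alone decides:* 5%.
- *Both must be significant:* at most 5%.
- *Either suffices, independent tests:* 1 − (1 − 0.05)² = 1 − 0.9025 = 0.0975, or 9.75%.
- *Either suffices, any dependence:* at most 0.05 + 0.05 = 0.10.
- *Either suffices, correlated test statistics (bivariate normal):* 9.5%, 9.1%, 8.3% and 7.0% for assumed correlations of 0.3, 0.5, 0.7 and 0.9.

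**4. Power under the ways of settling it** (d = 0.91, 20 per group).

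- *AES as sole primary outcome:* 80.1%, unchanged.
- *Fixed order, AES first:* also 80.1% for the AES.
- *Equal split, 0.025 each:* 70.6% for the AES, a loss of 80.1 − 70.6 = 9.5 points.
- *Both required:* about 0.801 × 0.801 = 64%, if the Zarit test also had 80.1% power and the two were independent. Both conditions are assumptions.

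**5. The test for burden.** The aim concerns a difference between arms. A paired t or signed-rank test estimates change within the people analysed. Run in one arm or in both pooled, it contains no between-arm contrast. Run separately in each arm, it yields two p-values whose comparison is not a test of the difference.

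**The case against.** A condensed article may leave multiplicity rules to a full protocol or analysis plan that is not shown, and the aims are worded as exploratory. This stands in part: the missing combination rule is not by itself a fault. But a later plan cannot make both statements in this article true, and the article also states a hypothesis, a significance level and a power figure.

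A reader might infer that the trial's error rate is not 5%. The documents do not support that as a flat statement. It exceeds 5% only if success on either outcome counts, and no such rule is given. Nor does 9.75% strictly describe the plan as written, since the named test for relatives is not a between-group test at all.

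A reader might also infer that splitting alpha would take AES power from 80% down to 52–59%. That mixes in drop-out. With the stated 20–30% loss, 16 or 14 per group remain, and power at 0.05 is already 70.2% or 64.0%. At 0.025 it is 58.9% or 52.0%, so the split itself costs about 11 to 12 points there.

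Nor did the power calculation set the sample size: the article says 40 was the most that two robots could serve. The power statement shows which outcome the authors had in mind, no more.

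Finally, the sentence on between-group analysis of secondary outcomes could be stretched to cover the Zarit. But the Zarit is not listed as secondary, and relatives' outcomes have their own sentence naming a different analysis.

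**Conclusion.** The contradiction stands and can be read directly from the article. The hypothesis, primary analysis and power statement point to motivation alone, while the aims and measurements add care burden. The consequence is an undefined criterion for a positive trial. The inflation is conditional: 9.75% with independent tests and at most 10% if either outcome suffices, about 7.0% to 9.5% for correlations of 0.9 to 0.3, and no more than 5% under the other two readings. Separately, the analysis named for relatives' outcomes does not answer the between-group aim for burden, whichever way the hierarchy is settled. The matter should be corrected before analysis. It does not invalidate the design.

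**What to change.** 1. In Primary Aims and Primary Outcome Measurements, name the AES as the sole primary outcome, matching the hypothesis, primary analysis and power statement.
2. Make the Zarit the first secondary outcome. Replace the paired test for it with a between-group comparison of post-intervention burden adjusted for baseline Zarit.
3. Test the Zarit at 0.05 only if the AES between-group test is significant. Otherwise report the estimate with its confidence interval. This order keeps the family-wise error for the two outcomes at 5% and leaves AES power unchanged.
4. Record the change, its reason and its date in the trial register before any unblinded analysis. The Measurements section promises register entries for changes in measurement methods. That does not cover a change of outcome hierarchy, so an explicit entry is needed.

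Keeping two primary outcomes would also remove the contradiction, provided the success rule, the alpha for each and a between-group test for burden are stated. It would cost power under an equal split or a both-required rule, as shown above.

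Cost of the recommended change: no new participants or visits. The Zarit could be claimed only after a positive AES, and moving a listed primary outcome down during a running trial must be justified openly.

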#### Secondary Aims

There are several secondaru aims of this study, one of which is exploring the effect of Coach Robot Pepper on acceptance, usability, quality of life, cognition, mobility, depression, behavioral problems, and care dependency of people with dementia versus the tablet PC–based training. We would also like to explore the effect of Coach Robot Pepper on depression, quality of life, affect and acceptance, and usability of relatives versus the tablet PC–based training. There will also be a supplementary investigation of the acceptance and usability of robot Pepper and the tablet PC–based training in dementia trainers and caregivers, a supplementary observation of people with dementia to get an insight into how to handle a robot and the tablet PC–based training in home care (including usability), and supplementary interviews (focus groups or individual interviews) to obtain a deeper understanding of the experience (including usability) of all participants using Coach Robot Pepper in home care.

The description of the study protocol follows the Standard Protocol Items: Recommendations for Interventional Trials guideline [29].

## Methods

### Design

A mixed method study with embedded design will be performed. The quantitative part will be a randomized, controlled, parallel, two-arm study, and the complementary qualitative part will include semistructured, guideline-based interviews. This design was chosen to not only obtain quantitative results but also to get a deeper insight into the experiences of using a SAR in home care for people with dementia.

### Setting and Sample

#### Setting

This study will be performed in the private households of people with dementia living in Styria, which is one of the 9 federal states of Austria, with 1,239,153 inhabitants [30] in 540,800 private households and an average household size of 2.25 people [31].

#### Sample

We will include people with mild and moderate dementia as the main sample. We will also include their main relative as well as their nursing staff (nurses and nursing assistant) and dementia trainers. The inclusion criteria are presented in Textbox 1.

Inclusion criteria.
**Persons with dementia**
adultsliving at homeall types of dementia (except frontotemporal dementia)mild or moderate dementia (Mini Mental State Examination 10 and above)mild dementia: living alone or with a relative at home (if alone, the relative should live in the neighborhood and be in daily contact with the person with dementia)
moderate dementia: living with a relative at homereceive professional or nonprofessional care or no carespeak and understand Germanhave no physical, auditory, or visual restrictions, which would make the application of the interventions impossibledo not take any dementia-specific medication or have been taking dementia-specific medication for at least 3 months; condition stable and no change expected during the study perioddo not take antipsychotics and antidepressants or have been taking them for at least 14 days before study startchildren and pets in the household after previous individual discussion
**Relatives**
relatives of the participating people with dementia (adults)living or not living with the person with dementia in the same household (in the case of moderate dementia, relatives must live in the same household)person with dementia receives or does not receive professional carerelative provides or does not provide careif the people with dementia receive paid 24-hour care (regardless of whether they have mild or moderate dementia), a relative still has to be recruited as a participant (this relative must live in the same house or household and be in daily contact with the person with dementia)speak and understand German
**Nursing staff**
adultsnurses or nursing assistantsspeak and understand German
**Dementia trainers**
adultstrained as Morbus Alzheimer Syndrome trainertrain the participants with dementia at homespeak and understand German

